### 2.12. Protection of Participants

#### 2.12.1. Ethical Approval and Registration

This study protocol was approved by the ethics committee at Kyung Hee University Korean Medicine Hospital (KOMCIRB-160212-HRBR-004). It will be performed in accordance with the standards of the International Committee on Harmonisation on Good Clinical Practice and the revised version of the Declaration of Helsinki. This trial was registered via US National Institutes of Health Clinical Trials registry (ClinicalTrials.gov) on 15 July 2016 (identifier: NCT02844452). The trial registration was conducted after the start of participant recruitment due to delays in the preparation of registration.

#### 2.12.2. Participant Safety

During each visit, unanticipated problems or adverse events related to acupuncture treatment will be reported by participants and documented by study staff. Acupuncture treatment has been reported as a safe treatment rarely causing adverse effects; common adverse effects caused by acupuncture treatment include bleeding, hematoma, and pain [66]. Any unfavourable or unexpected signs related to study treatment or procedures will be compiled on paper, managed under the care of practitioners, and reported to institutional and other oversight agencies as appropriate.

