### 2.7. Blinding and Code Breaking

Participants and the outcome assessor will be blinded to the treatment allocation in this trial. Since it is impossible to blind the Korean Medicine Doctors (KMDs) who will give acupuncture treatments, they will be excluded from performing the outcome measurements or analysing data. To ensure participant blinding, an eye patch will be applied to patients during the acupuncture treatment, and they will be unable to see the practice procedures. All the acupuncture treatments, regardless of group assignment, will utilise the Park sham device (AcuPrime Co., Ltd., Exeter, UK), which is applied at the acupoints to block participants from seeing whether or not the acupuncture needles penetrate the skin [21]. The acupuncture needles and device will be maintained in place for 15 min in all treatment groups. If a participant has a serious adverse event and immediate cessation of acupuncture treatment is required, the blinding code will be broken.

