#### 2.8.2. Verum Acupuncture Group 1 (VA1)

Participants assigned to the VA1 will receive 12 acupuncture sessions over 4 weeks, that is, 3 days/week. A telephone interview will take place two weeks after the end of treatment to collect data on the severity of pruritus symptoms, amount of TCS used, and adverse effects. Participants' final visit will occur 4 weeks after the end of treatment. No other intervention will be permitted during the study period.

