#### 2.8.4. Sham Acupuncture Group (SA)

Participants assigned to the SA group will receive 8 acupuncture sessions over 4 weeks, that is, 2 days/week. Sham acupuncture treatment will be conducted on 6 control points: a point 1 to 2 cm proximal and 1 cm medial to LI7, a point 1 cm proximal and 1 cm medial to LI11, and a point 1 cm proximal and 1 cm lateral to ST36, each bilaterally. Instead of intradermal needles, the same sized stainless steel rings without needles, that is, nonpenetrating intradermal needles, which were designed and validated for blinding for our study, will be attached to three control points: a point 1 cm proximal and 1 cm medial to LI11, bilaterally, and finger point in the ear, contralaterally [25]. Unlike VA1 and VA2, fixed acupuncture treatments will be given, but questions about symptoms, TCS, and adverse effects will be asked to participants in this group. A telephone interview will also be given two weeks after the end of treatment to collect data on the severity of pruritus symptoms, amount of TCS used, and adverse effects. After the 4-week treatment period, participants will return for a final visit at 4 weeks after the end of treatment, identical to VA1 and VA2.

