●: conducted on every participant of this study, both AD patients and healthy controls; ○: conducted on AD patients of this study, not on healthy controls; ⊗: conducted on AD patients, but with different frequency on groups. That is, VA1 receives acupuncture treatment or checks adverse events 3 days a week, VA2 2 days a week, and SA 2 days a week; ☏: a telephone interview will be conducted on AD patients of this study, not on healthy controls; AD, atopic dermatitis; CES-D, Center for Epidemiologic Studies-Depression Scale; Cold-Heat, cold-heat pattern identification based on diagnosis in Traditional Korean Medicine; DLQI, Dermatology Life Quality Index; EASI, Eczema Area and Severity Index; POEM, Patient Oriented Eczema Measure; PPT, Pain Pressure Threshold; SCORAD, SCORing Atopic Dermatitis; STAXI, state-trait anger expression inventory; TCS, topical corticosteroid.

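### Section 2.12.2 ties adverse event recording to relatedness, while Table 2 schedules adverse events without that condition, so events thought unrelated may go unrecorded

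*Protocol article*

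**What the plan says.** Two sentences in section 2.12.2 (Participant Safety) govern what is recorded. For each visit: "unanticipated problems or adverse events related to acupuncture treatment will be reported by participants and documented by study staff". For compilation: "Any unfavourable or unexpected signs related to study treatment or procedures will be compiled on paper, managed under the care of practitioners", followed by reporting to oversight bodies as appropriate. Both carry a relatedness condition.

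Other places in the article are worded differently:

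- Table 2 has a row for adverse events covering treatment weeks 1 to 4, the week 6 telephone call and the week 8 visit, with no mention of relatedness. Its footnote sets the frequency: "VA1 receives acupuncture treatment or checks adverse events 3 days a week, VA2 2 days a week, and SA 2 days a week".
- The telephone interview serves "to collect data on the severity of pruritus symptoms, amount of TCS used, and adverse effects" (section 2.8.2, with similar wording in 2.8.3 and 2.8.4).
- In the sham arm, "questions about symptoms, TCS, and adverse effects will be asked to participants in this group" (section 2.8.4).

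On blinding, section 2.7 states: "Participants and the outcome assessor will be blinded to the treatment allocation in this trial". Of the practitioners it says: "Since it is impossible to blind the Korean Medicine Doctors (KMDs) who will give acupuncture treatments". It therefore keeps them out of outcome measurement and data analysis.

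**The concern.** If an event must be related to treatment before it is documented, somebody judges causality before there is a record. Events put down to another cause may then leave no trace, and nobody can later review that decision.

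Two things are at stake. The first is completeness: harms not already associated with acupuncture are the ones most likely to be thought unrelated. The second is comparability. Verum patients receive 6 to 19 manual needles and 3 intradermal needles per session, 9 to 22 in all. Sham patients receive non-penetrating devices. Anyone who knows the arm could attribute the same complaint differently. Section 2.7 shields the outcome measures from the practitioner's knowledge of allocation, but the article describes no equivalent protection for the safety record.

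The trial is meant to inform the choice of regimen and the design of a larger trial, so event counts by arm are part of its useful yield.

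**Working it through.** The plan gives no safety figure to reproduce. The check is a comparison of texts, followed by simple arithmetic on what the rule could do.

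**Texts side by side**

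| Place | What is captured | Relatedness condition |
|---|---|---|
| 2.12.2, visits | Unanticipated problems or adverse events | Yes, to acupuncture (it may attach only to the events) |
| 2.12.2, compilation | Unfavourable or unexpected signs | Yes, to treatment or procedures |
| Table 2 | Adverse events | None stated |
| 2.8.2 to 2.8.4, telephone | Adverse effects | None stated separately, though the term itself suggests a cause |

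Table 2 settles when events are asked about. Section 2.12.2 is the only place that says which events are documented and compiled, and there the condition applies.

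**Weight of one event.** 30 patients allocated 1:1:1 gives 30 / 3 = 10 per arm. One patient whose event is not recorded changes the arm's rate by 1 / 10 = 10 percentage points.

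**What the filter does.** Recorded rate = true rate × probability that an event is called related. The documents give neither quantity, so the values below are assumptions. The true rate is the same in verum and sham.

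| True rate | Called related, verum / sham | Recorded, verum / sham | False difference |
|---|---|---|---|
| 0.2 | 0.8 / 0.8 | 0.16 / 0.16 | 0 |
| 0.3 | 0.8 / 0.8 | 0.24 / 0.24 | 0 |
| 0.5 | 0.8 / 0.8 | 0.40 / 0.40 | 0 |
| 0.2 | 0.8 / 0.4 | 0.16 / 0.08 | 0.08 |
| 0.3 | 0.8 / 0.4 | 0.24 / 0.12 | 0.12 |
| 0.5 | 0.8 / 0.4 | 0.40 / 0.20 | 0.20 |

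Equal attribution loses events in every arm but creates no difference where the true rates are equal. A false difference needs attribution that varies by arm.

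**Event contacts scheduled after baseline.** These are treatment sessions plus the telephone call plus the final visit:

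- VA1: 12 + 1 + 1 = 14
- VA2: 8 + 1 + 1 = 10
- SA: 8 + 1 + 1 = 10

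The ratio is 14 / 10 = 1.4. A higher count in VA1 could therefore reflect more treatment, more asking, or both.

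**The case against.** The case against has several sound parts, and they limit how far the point goes.

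- A reader might infer that events enter the record only if judged related. Table 2 and the telephone interviews do not state that filter, and the sham arm is actively asked. What stands is an inconsistency between these places and 2.12.2.
- A reader might infer that an unblinded practitioner decides relatedness before anyone blinded is involved. The text does not say so. Participants report the events, and they are blinded. Study staff, whose blinding is not stated, document them. Practitioners are named for managing the signs, not for judging cause.
- A reader might infer that an unexpected harm cannot appear. Section 2.12.2 names unanticipated problems and unexpected signs, and its list of bleeding, haematoma and pain describes common effects, not a closed set.
- A flare of dermatitis would not vanish. Itch VAS, SCORAD, EASI and POEM are taken weekly during treatment and at week 8, and topical steroid use is tracked. It might lack an adverse event label, but it would be visible. Skin infection is the better example.
- Section 2.11.2 specifies no safety comparison between arms, so no planned test is compromised.
- A condensed article may leave the causality procedure and form fields to the full protocol. Their absence is therefore not the fault. The fault is the recording rule that the article does state, and no other sentence overrides it.

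**Conclusion.** The point holds in a limited form. Both operative sentences of 2.12.2 make relatedness a condition of recording, Table 2 does not, and the places need to be reconciled. Followed literally, 2.12.2 would under-count adverse events in every arm.

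It is tempting to go further and say that the verum-sham safety comparison is distorted. The documents do not support that. Distortion needs arm-dependent attribution, which they neither show nor exclude. The false differences of 8 to 20 percentage points in the working rest on assumed attribution of 0.8 against 0.4 and assumed true rates of 0.2 to 0.5. The figures that rest on the documents alone are the 10 percentage points per patient-event, from 10 per arm, and the 14 against 10 scheduled contacts.

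**What to change.** In 2.12.2, delete both relatedness conditions and state that all adverse events in all arms are recorded regardless of suspected cause, consistent with Table 2.

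Record relatedness afterwards in a separate field. Where possible it should be judged by existing study staff who are blinded to allocation and are not the SCORAD/EASI assessor. The sham is non-penetrating, so a report of bleeding or haematoma at a needle site would point to verum and could unblind the one nurse who scores the outcomes. The person judging should also not see the session count, since only VA1 has 12 sessions.

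Report all events by arm first and the related subset second, and state beside the table that scheduled event contacts were 14 in VA1 and 10 in VA2 and SA.

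The cost is two protocol sentences and one case report form field. The downside is a longer event list that includes trivial unrelated complaints. No treatment or visit changes.

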#### 2.12.3. Quality Control

All participating KMDs and outcome assessors will be trained before the beginning of the trial to ensure consistent quality of practices. The training program will cover diagnoses, inclusion and exclusion criteria, location of the acupoints, acupuncture manipulation techniques, measurement of PPT, and filling out case report forms. Participants who discontinue or who withdraw consent will also be thoroughly documented. This study will be monitored by the AMSRC and periodic monitoring will ensure the accuracy and the quality of this study. We checked Standard Protocol Items: Recommendations for Interventional Trials (SPIRIT) to improve the quality of clinical trial protocols (see Additional File 1 in Supplementary Material available online at https://doi.org/10.1155/2017/1926806) [67].

#### 2.12.4. Confidentiality

After enrolment, participants' personal information will be accessible only to the investigator. Research data and blood samples will be identified by a unique code to protect confidentiality during and after the trial. All study personnel completed training in protection of personal health information.

### 2.13. Protocol Amendments

If a protocol modification is required (such as due to an unanticipated problem or adverse event), the representatives of Kyung Hee University Korean Medicine Hospital and the AMSRC will discuss the matter fully to take the appropriate steps.

## 3. Discussion

A recent systematic review failed to identify any RCTs on acupuncture as treatment for AD, as it has not been extensively researched [15]. We describe a protocol for a randomised, sham-controlled feasibility trial comparing two VA groups with different treatment schedules with SA to assess the effectiveness of acupuncture in individuals with AD, to be conducted in clinical settings in Korea. The aims are to evaluate whether the proposed acupuncture treatments warrant further investigation for improvement of symptoms, mental health, and quality of life and whether a relationship can be established between certain biomolecules and the development of AD by comparing levels in the blood of individuals with AD to healthy controls.

Determining an optimal dose of acupuncture treatment involves complex decision making [68, 69]. Clinical practice and patients' acceptability should be carefully considered when comparing two different dosages/schedules (3 days weekly versus 2 days weekly for 4 weeks). Our study results will elucidate which regimen produces maximal effectiveness and which schedule participants prefer, which is of importance to practitioners and educators.

We will limit enrolment to individuals with mild to moderate AD. Since KMDs usually treat severe cases with more intensive combinations of treatment, such as acupuncture and herbal medicine or acupuncture and hospitalisation, we selected acupuncture alone in order to detect differences between treatments without introducing other confounders; in addition, rescue medication will be permitted as we believe that this strategy reflects real world practice.

A battery of outcome measures will be used in our study since it is exploratory in nature. We will investigate the effects of acupuncture treatment on AD symptom improvement with a particular focus on antipruritic effect, measured using itch VAS, SCORAD, EASI, and POEM. Information on rescue medication use and quality of life will also be collected. For pattern identification in Korean Medicine, the AD pattern and Cold-Heat questionnaires, along with PPT, will be administered. CES-D and STAXI will examine potential anxiolytic and stress-relieving effects of acupuncture. Through credibility testing, the feasibility of participant blinding to treatment assignment will be thoroughly examined. Some may argue that nonspecific effects may unnecessarily increase in our trial by the increased attention due to a variety of outcome measures. The outcome measures, however, will be given to the participants in all three groups which will make it unlikely for one specific group to experience a larger nonspecific benefit due to the increased attention. We will nevertheless carefully examine whether there will be additional nonspecific benefits in any group and the feasible outcome measures will be selected to work for a main trial. Finally, our study will provide valuable data regarding treatment of AD with acupuncture, but also relative to identifying potential biomarkers associated with its development.

Establishing an adequate sham control is essential in an RCT of acupuncture. We will utilise a nonpenetrating sham acupuncture and nonpenetrating intradermal needles as a control group, which receive sham treatment twice a week for 4 weeks. There has been a long debate about the specific effect of acupuncture: acupuncture works mainly via a placebo effect [70]; or tested sham acupuncture controls so far may not be completely inert [71, 72]. The sham control in our study was designed to minimise a specific physiological effect that may be induced by needle insertion and to avoid specific acupuncture points in the body and the ear. In addition, the number of treatment sessions in the control group was set as twice weekly to minimise other nonspecific benefits such as doctor-patient interaction and the Hawthorne effect; this is feasible due to appropriate blinding techniques.

Attempts have been made to identify biomarkers in order to measure the specific effects of acupuncture and to better understand its mechanism of action [73–75], but no reliable marker has yet to be established due to the lack of sensitivity and/or specificity. Recently, attention has increasingly focused on serum circulating miRNAs as reliable noninvasive or minimally invasive biomarkers because they are abundant, extremely stable in blood, and differentially expressed in various diseases [76]. Hence, we propose exploring novel miRNA-based candidates in association with the antipruritic effect of acupuncture, providing new opportunities to identify valuable biomarkers for the specific effects of acupuncture.

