## Abstract

This study aims to test the feasibility of a randomised clinical trial to evaluate how acupuncture affects atopic dermatitis (AD) symptoms and quality of life and to explore potential biomarkers that may be associated with AD. It is a sham-controlled trial in which 30 eligible patients will be randomly allocated in a 1 : 1 : 1 ratio to one of three groups: verum acupuncture (VA) group 1 (3 times weekly for 4 weeks); VA group 2 (twice weekly for 4 weeks); or sham acupuncture group (SA; twice weekly for 4 weeks). SA will consist of nonpenetrating acupuncture. Outcome measures will include the Visual Analogue Scale for itch, SCORing Atopic Dermatitis, and Eczema Area and Severity Index to evaluate AD symptoms improvement along with the Patient Oriented Eczema Measure and Dermatology Life Quality Index to assess quality of life. Measures will be collected at baseline, once weekly during the treatment period, and after a 4-week follow-up period. Blood collection will be at baseline and 4 and 8 weeks after treatment and compared with healthy controls. Illumina sequencing will be used to profile microRNA expression in each group to explore candidate microRNA biomarkers for specific effects of acupuncture in patients with AD. This trial is registered via US National Institutes of Health Clinical Trials registry (ClinicalTrials.gov) on 15 July 2016, identifier: NCT02844452.

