#### 2.10.12. Credibility Test

To assess the credibility of the acupuncture treatment used in this study, participants will complete the credibility questionnaire at baseline, at 4 weeks (after the termination of treatment period), and at 8 weeks (after the end of follow-up period) [47, 48].

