*(3) Treatment regimen*	*(3a) Number of treatment sessions* (i) 8 or 12 sessions according to the allocated group *(3b) Frequency and duration of treatment sessions* (i) Twice or 3 times a week for 4 weeks, 20 minutes for each session

*(4) Other components of treatment*	*(4a) Details of other interventions administered to the acupuncture group (e.g., moxibustion, cupping, herbs, exercises, lifestyle advice)* (i) Lifestyle advices will be given to all participants (ii) Corticosteroids will be allowed as a rescue medicine of severe pruritus through the consensus of the KMD in charge of this study and the pharmacist working for Kyung Hee University Korean Medicine Hospital *(4b) Setting and context of treatment, including instructions to practitioner and information and explanations to patients* (i) A university hospital (ii) Participants will be informed about acupuncture treatment in the study as follows: “In this study, you will be randomly allocated to verum acupuncture treatment or sham acupuncture treatment and acupoints for AD will be selected based on traditional Korean medicine textbook and AD-related reports. Also, additional acupoints can be used according to individual conditions.”

*(5) Practitioner background*	*(5) Description of participating acupuncturists (qualification or professional affiliation, years in acupuncture practice, other relevant experience)* (i) A KMD who has a license and at least two years of clinical experience in dermatologic disorders. He attended 10 hours of training and simulation workshop to ensure that he is able to provide identical acupuncture treatment in accordance with a predefined protocol

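### The credibility questionnaire, given only at baseline and at weeks 4 and 8, is weak and confounded evidence on participant blinding, not the thorough test the Discussion promises

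*Protocol article*

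**What the plan says.** Section 2.7 sets the standard: "Participants and the outcome assessor will be blinded to the treatment allocation in this trial". The only check on this that the article describes is in section 3 (Discussion): "Through credibility testing, the feasibility of participant blinding to treatment assignment will be thoroughly examined".

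Section 2.10.12 gives the same instrument a different purpose: "To assess the credibility of the acupuncture treatment used in this study, participants will complete the credibility questionnaire at baseline". The later ratings come "at 4 weeks (after the termination of treatment period), and at 8 weeks (after the end of follow-up period". Table 2 agrees: the credibility test is marked at baseline, week 4 and week 8, and at no week in between.

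The symptom measures run on a denser schedule. According to the Abstract, "Measures will be collected at baseline, once weekly during the treatment period, and after a 4-week follow-up period". In Table 2 this covers itch VAS, SCORAD, EASI, POEM and DLQI at weeks 1 to 4 and week 8.

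Table 1 (item 4b) shows what patients are told: "you will be randomly allocated to verum acupuncture treatment or sham acupuncture treatment". The Discussion also leans on blinding when it defends giving sham only twice weekly: "this is feasible due to appropriate blinding techniques".

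**The concern.** Credibility is belief in a treatment. Blinding concerns belief about which treatment one received. The two are related, but a patient can find a treatment credible and still suspect sham, or can doubt a treatment while certain it was real.

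The timing adds to the difficulty. The baseline rating precedes the first session, so it cannot reflect anything the procedure gives away. The next rating comes after four weeks in which each patient has felt the itch improve or not, so it mixes cues from the procedure with perceived benefit.

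This matters because itch VAS, POEM, DLQI and the subjective items of SCORAD are patient-reported, and the study is meant to inform a large sham-controlled trial. If credibility ratings are read as a test of blinding, the main trial could inherit a sham procedure whose masking was never directly checked, or could reject one that masked well.

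**Working it through.** The article gives no figure for the blinding assessment, so there is none to reproduce. The first step compares texts. The others are illustrations of scale using normal approximations.

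**Inputs.** 30 patients allocated 1:1:1 (Abstract), so 10 per arm. Expected dropout 20% (section 2.11.1): 30 × 0.8 = 24, or 8 per arm if losses are even. Two-sided significance level 0.10 with 90% CIs (section 2.11.2), so z = 1.645.

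**1. Purpose and timing.**
- Section 2.10.12 names credibility as the purpose and does not mention blinding. The Discussion names blinding.
- Of the three ratings, one precedes all needling and two follow the whole treatment course. None falls in between.
- No item on perceived assignment is described, although patients know they may receive verum or sham, so a guess could be asked.

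**2. What would a null credibility result show?** For two arms of n, the difference detectable with 80% power is (1.645 + 0.842) × √(2/n) SD.
- n = 10: 2.487 × 0.447 = 1.11 SD.
- n = 8: 2.487 × 0.500 = 1.24 SD.
- Power for a 0.5 SD difference is about 30% (n = 10) or 26% (n = 8).

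Finding no difference would therefore give little reassurance.

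**3. What would a positive result show?** Assume perfect blinding, a true symptom effect of d SD, and a correlation ρ between improvement and week-4 credibility. The induced credibility difference is ρ × d. The values of d and ρ are assumptions, since the article gives none.

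| ρ | d | Induced difference (SD) | Chance of significance, n = 10 |
|---|---|---|---|
| 0 | any | 0 | 10% |
| 0.3 | 0.5 | 0.15 | 12% |
| 0.5 | 0.8 | 0.40 | 23% |
| 0.7 | 1.0 | 0.70 | 47% |

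A difference at week 4 could thus come from unblinding or from benefit, and the rating does not separate them.

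**4. What would a direct question give?** The Bang index in one arm, if nobody answers do not know, is 2p − 1, where p is the proportion guessing correctly. Its standard error is 2 × √(p(1 − p)/n), which is √(1/n) at p = 0.5.
- n = 10: 1.645 × √(1/10) = 0.52.
- n = 8: 1.645 × √(1/8) = 0.58.

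The scale runs from −1 to +1. In concrete terms, 8 correct of 10 gives an index of 0.60 with half-width 1.645 × √(0.64/10) = 0.42, which excludes zero. With 7 of 10 the index is 0.40 with half-width 1.645 × √(0.84/10) = 0.48, which does not.

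**The case against.** A reader might go further and infer that the plan cannot show anything about blinding, or yields no data on it. That is not supported. Credibility is collected in all three arms at weeks 4 and 8, and comparing arms gives weak, indirect evidence on whether sham was as believable as verum. Section 2.10.12 also cites the questionnaire without reproducing its items, so an assignment guess may sit within it or in the full protocol. What can be said is that the article describes none.

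A reader might also infer that the later ratings are given after outcomes are known. The documents do not say so. No results are disclosed to patients, the order of measures within the week-4 visit is not stated, and at week 4 the week-8 outcome is still to come. Patients have only felt their own symptoms, which is enough for confounding.

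Nor do the documents support the idea that sham looks different. Section 2.7 describes an eye patch and the Park device in every group, and section 2.8.4 describes needle-free rings of matching size, said to have been validated for blinding. Fixed points are a weak cue, since verum patients may also receive only the six basic points. Any cue is more likely to come from sensation, because verum needling seeks de qi.

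It is also fair that blinding assessment is absent from the aims in section 2.1. The promise rests on one Discussion sentence, though the sham schedule is defended by the same blinding.

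Finally, a guess asked at week 4 would share the confounding described here. That objection stands and determines the timing of the remedy.

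**Conclusion.** The point holds in limited form. The article presents credibility as a thorough examination of blinding, but the method it describes measures something else, at times that either precede the procedure or follow the felt response. Weeks 4 and 8 give indirect evidence, mixed with perceived benefit.

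The size is illustrative: about 30% power for a 0.5 SD credibility difference at 10 per arm, and a 12% to 47% chance of a significant difference under perfect blinding against a nominal 10%. The second range depends on the assumed effect (0.5 to 1.0 SD) and correlation (0.3 to 0.7).

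The conclusion on purpose and timing does not depend on those values. It does depend on the cited questionnaire containing no perceived-assignment item. If it contains one, the sponsor need only say so, but the lack of any rating between the first session and week 4 remains. The change is worth making because it is cheap and bears on a question that the article sets for itself.

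**What to change.** - Unless the cited questionnaire already includes it, add one perceived-allocation question (verum, sham or do not know, with the reason) after the first session or at the end of week 1. Make this the main blinding check.
- Report a Bang index per arm with 90% CI, and state beforehand that at 8 to 10 per arm it can reveal only gross unblinding.
- If the question is repeated at week 4, treat that answer as secondary because it is confounded with response.
- Move or add a credibility rating to follow the first session.
- Reword the Discussion so that credibility alone is not called a thorough test of blinding.

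The cost is one extra question and one short rating at existing visits, with a small risk that asking draws attention to allocation. If treatment has already finished, the rewording and a stated limitation can still be made.

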#### 2.8.3. Verum Acupuncture Group 2 (VA2)

Participants assigned to the VA2 will receive 8 acupuncture sessions over 4 weeks, that is, 2 days/week. A telephone interview will be given two weeks after the end of treatment to collect data on the severity of pruritus symptoms, amount of TCS used, and adverse effects. Participants' final visit will occur 4 weeks after the end of treatment. No other intervention will be permitted during the study period.

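### The sham arm is session-matched to VA2 only (8 versus 8), so if VA1 (12 sessions) is the arm chosen for comparison, the verum-sham difference may partly reflect extra sessions.

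*Protocol article*

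**What the plan says.** The treatment schedules are in Section 2.8 of the protocol article:

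- VA1: "Participants assigned to the VA1 will receive 12 acupuncture sessions over 4 weeks, that is, 3 days/week".
- VA2: "Participants assigned to the VA2 will receive 8 acupuncture sessions over 4 weeks, that is, 2 days/week".
- SA: "Participants assigned to the SA group will receive 8 acupuncture sessions over 4 weeks, that is, 2 days/week".

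Table 1, item 3b, gives one session length for all arms: "Twice or 3 times a week for 4 weeks, 20 minutes for each session". Section 2.8.1 has a single practitioner deliver every session. The notes to Table 2 have adverse events checked three days a week in VA1 and two in VA2 and SA.

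Section 2.11.2 names one pairwise verum-sham comparison for therapeutic effect, between SA and the better-performing verum arm. Section 2.10.14 and the Figure 2 legend apply the same rule to miRNA. Section 2.2 hypothesises that the three-times-weekly schedule will do better than the twice-weekly one. Sections 2.11.1 and 2.11.2 say the data will inform the sample size of a larger trial.

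The Discussion gives the reason for the sham frequency: "the number of treatment sessions in the control group was set as twice weekly to minimise other nonspecific benefits such as doctor-patient interaction". It adds the Hawthorne effect and says that blinding makes this feasible.

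**The concern.** A sham control isolates needling only if everything else, including the number of treatment encounters, is alike in the two arms compared. Here that is true of VA2 against SA and not of VA1 against SA. Setting the sham arm at the lower frequency reduces nonspecific benefit in the control group alone. Blinding to skin penetration does not change how often a participant is treated.

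The selection rule matters because it decides which contrast is reported. The matched comparison exists in the design but gives way to the unmatched one whenever VA1 looks better, and any benefit from extra sessions would itself make VA1 look better.

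Three uses are at stake: the interpretation of self-reported outcomes such as itch VAS, POEM and DLQI; the effect size used to plan the main trial; and the labelling of miRNA differences as related to acupuncture.

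**Working it through.** **Session counts.** Days per week x 4 weeks: VA1 3 x 4 = 12; VA2 and SA 2 x 4 = 8. These reproduce the stated 12, 8 and 8.

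**Planned session time (20 minutes each, Table 1).**

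- VA1 versus SA: 240 versus 160 minutes; 12/8 - 1 = +50%, or 80 minutes.
- VA2 versus SA: 160 versus 160 minutes; no excess.

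**Limits on reading this as contact time.** Needles are retained for 15 of the 20 minutes, and the documents do not say whether the practitioner interacts with the participant then. Counting only the other 5 minutes gives 12 x 5 = 60 versus 8 x 5 = 40: the same ratio, but a gap of 20 minutes rather than 80. The efficacy assessments, the telephone call and the final visit follow one schedule in all arms, so the excess in total staff contact is below 50%.

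**Compliance (Section 2.9).** The minimum is 10 of 12 sessions for VA1 and 6 of 8 for SA. At both minima the ratio is 10/6 = 1.67. Among compliant participants it can run from 10/8 = 1.25 to 12/6 = 2.0.

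**Possible size on itch VAS (assumption only).** Suppose 8 sham sessions yield N points of nonspecific improvement, and this grows with sessions somewhere between not at all and in proportion. The VA1-SA bias is then 0 to (12/8 - 1)N = 0 to 0.5N. With N = 2, that is 0 to 1 point. The documents supply neither N nor the growth.

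**How the selection rule interacts with a session effect (illustration).** Assumptions: normal outcomes with SD 1; no needling effect in any arm; a benefit from extra sessions in VA1 only; the verum arm with the better mean is chosen and tested against SA by the plan's Mann-Whitney test at two-sided 0.1; 6,000 simulated trials per row. Arm size is 30/3 = 10, or 10 x 0.8 = 8 after the planned 20% dropout.

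| n per arm | Assumed session benefit (SD) | VA1 chosen | Chosen arm vs SA significant | VA2 vs SA significant | Mean difference, chosen arm vs SA (SD) |
|---|---|---|---|---|---|
| 10 | 0 | 48.8% | 8.4% | 8.6% | 0.17 |
| 10 | 0.2 | 66.5% | 13.2% | 9.2% | 0.29 |
| 10 | 0.3 | 74.7% | 16.9% | 9.7% | 0.37 |
| 10 | 0.5 | 86.8% | 28.0% | 9.0% | 0.54 |
| 8 | 0 | 49.6% | 8.0% | 8.5% | 0.19 |
| 8 | 0.2 | 65.0% | 11.2% | 8.2% | 0.31 |
| 8 | 0.3 | 71.4% | 14.0% | 7.4% | 0.39 |
| 8 | 0.5 | 84.7% | 22.1% | 8.3% | 0.54 |

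VA2 versus SA has no true effect in any row, so its variation is simulation noise. The rows with zero session benefit show that choosing the better arm inflates the estimate even without a session effect (0.17 to 0.19 SD). That is a separate problem, which the same fix removes.

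**Adverse events.** Three against two checks a week gives 12 against 8 over treatment. At an equal rate r per session, expected counts are 12r and 8r, so raw counts per patient differ by 50% with no difference in risk per session.

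**The case against.** Much of the case on the other side stands. This is a 30-patient feasibility trial with no designated primary outcome, and comparing schedules is one of its aims. The matched arm, VA2, is already in the design. The problem arises only if VA1 is selected, and part of the exposure comes from the data-driven choice of arm. The Discussion also promises to examine nonspecific benefits by group, although it names no analysis that would separate session number from needling.

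Three stronger readings are tempting, and the documents do not support them.

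- *That the Discussion contradicts itself.* It argues that the measures go to all groups, "which will make it unlikely for one specific group to experience a larger nonspecific benefit due to the increased attention". That sentence answers a worry about attention arising from the many outcome measures. Table 2 bears it out for the efficacy measures, which follow one schedule in every arm. It makes no claim about treatment sessions.
- *That participants are unblinded by their visit frequency.* Three sessions a week occur only in a verum arm, so someone who knew all the schedules could infer allocation. But the participant information quoted in Table 1, item 4b, does not disclose the schedules, and the consent pages are not available here. Credibility is also tested at baseline, 4 and 8 weeks.
- *That VA1 receives 50% more therapist contact and its result is therefore biased.* The 50% is planned session time. Whether, and by how much, it shifts outcomes is unknown.

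What none of this answers is that the named verum-sham comparison can be the unmatched one, and the hypotheses expect it to be.

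**Conclusion.** The point holds in a conditional form. If VA1 is the arm compared with SA, the contrast carries 12 against 8 planned sessions (+50% planned session time), and the resulting effect size may partly reflect additional sessions. The stated reason for twice-weekly sham does not address this. VA2 versus SA is free of the session difference, though not of every procedural one: verum participants receive 6 to 19 manual needling points per session, against 6 fixed sham points.

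The session counts and the 50% come directly from the documents. The size of any bias does not; the VAS range and the simulation rest on assumed session effects and include zero. Given the exploratory purpose, this should be corrected because the estimates feed the main trial, but it does not undermine the feasibility aims.

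**What to change.** 1. In Sections 2.10.14 and 2.11.2 and the Figure 2 legend, replace the rule that picks the better verum arm with VA2 versus SA as the prespecified session-matched sham contrast, for clinical outcomes and miRNA.
2. Name VA1 versus VA2 as the schedule contrast, understood as a comparison of whole schedules (needling and encounters together).
3. Also report VA1 versus SA, labelled as needling plus additional sessions. Carry that label with any effect size used for main-trial planning.
4. Report adverse events per session as well as per patient, and needling points per session by arm.
5. Reword the sham-frequency rationale in the Discussion to say that sessions are matched to VA2 and not to VA1. Leave the sentence about outcome measures as it is, since it covers assessments only.

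No treatment, visit or sample size changes. The cost is that session-matched sham evidence covers the twice-weekly schedule only, and VA2 versus SA still differs in the number of points.
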